### 2.10. Ethics

The protocol and template consent forms of this study have been approved by the Ethics Committee of Peking University Health Science Center (IRB00001052-18039). This study will adhere to the rules of the Declaration of Helsinki. Written informed consent will be obtained from all participants. Any modifications to the protocol, which may affect the conduct of the study or the participants’ benefits or safety, will be reported to the ethics committee. All information related to this study will be stored securely at School of Public Health of Peking University, in an area with limited access. Any information collected in this project will not be used for any other purpose. The investigators and associated research personnel will have access to information. 

### 2.11. Providing Suggestions

Suggestions for intelligent health management among the elderly in China will be provided. As the elderly have their own physical and mental characteristics and knowledge structure, recommendations on how to improve compliance, how to make the health management app more friendly, how to improve ease of use, how to create incentives, how to make the health knowledge and healthy lifestyle more acceptable to the elderly will be made based on the experiences during the conduction of the study. And if the result proves to be that the mobile-based lifestyle intervention is beneficial, it would provide a successful approach for the improvement of bodyweight, glucose and lipid metabolism and a scientific evidence for intelligent health management among the elderly in China.

### 2.12. Dissemination

The findings of this study will be disseminated via peer-reviewed publications specialized in nutrition or public health or presentations in relevant national and international conferences. The results will be available to the participants on request at a face-to-face meeting.

## 3. Trial Registration

The clinical trial registration number is ChiCTR1900023355 (http://www.chictr.org.cn/showproj.aspx?proj=38976). Date of registration: 23 May 2019.

## 4. Discussion

Overweight and obesity is associated with chronic diseases such as hypertension, diabetes and cardiovascular diseases [31]. These chronic diseases, as a main threat to health, led to three-quarters of deaths in China [32]. They have been considered to be closely influenced by unhealthy lifestyle [5], thus promotion of healthy lifestyles is a key strategy for reducing chronic disease risk [33]. Compared with traditional lifestyle intervention which is resource intensive and the effect decreases as time goes on [13,34], the new mobile-based lifestyle intervention, with its own advantages, is an attractive option for the prevention and control of chronic diseases. It has been shown that mobile-based lifestyle intervention is effective in the improvement of abnormal glucose and lipid metabolism and the control of obesity in several previous studies [16,17,35]. China has already entered an aging society phase with a large proportion of elderly people suffering from chronic diseases [36]. However, the effectiveness of mobile-based lifestyle intervention for the control of overweight, abnormal glucose and lipid metabolism among elderly population with a predisposition to chronic diseases is still unclear. This study intends to fill a gap in this field. 

The compliance of the subjects and the quality control will be the challenges during the study. Subjects in Group A and B will be asked to be intervened for as long as 3 months. Moreover, the elderly population whose learning ability to use mobile apps is not as good as the young may face more challenges. Poor utilization of app may cause the reduced effect of intervention [12]. In order to guarantee the compliance of them, convenient and effective methods of communication, such as telephone call, WeChat, short message and e-mail, between investigators and participants will be established. The investigators will fully explain the requirements and significance of this study to the subjects prior to the study, monitor their dietary and physical activity data and solve the problems they encounter in time. If a subject quits, the investigators will record the time and reasons timely. To ensure the quality control, participants will be trained to be familiarized with the content of questionnaires, the procedure and requirements of the trial prior to the study. If a participant fails to meet the requirements, their data will be eliminated and the reason will be recorded. Researchers will also be trained on the procedure of this trial, the content of the questionnaires and the requirements of laboratory tests. Indicators such as height, weight, waist circumference, hip circumference and blood pressure will be measured twice and the mean will be adopted as the final outcome. When filling in the FFQ, food models and photographic models will be used to enhance estimation accuracy. Blood samples will be stored at −80 degree centigrade immediately after collection to ensure the accuracy of laboratory tests. All laboratory measures will be operated by experienced staff. The conduct of this trial will be audited by a competent authority in the university every week, and the process will be independent from investigators and the sponsor. 

This study has both strengths and limitations. In terms of strengths, it will be designed as a randomized controlled trial which can reduce the selection bias and confounding influence. The consistence of baseline characteristics between groups will guarantee that the three groups are comparable. Secondly, the potential confounding factors such as age, sex, marital status, literacy, occupation, the state of chronic diseases, food intake, physical activity, living conditions and family and social support will be evaluated and included as covariates in the statistical analyses. What’s more, the prospective cohort design can avoid recall bias and improve the accuracy of the results. Fourthly, the sample size calculated will provide sufficient power to detect the effects. Fifthly, outcomes will be measured three times during the intervention and follow-up which will supply more detailed data. Finally, this will be a large multi-center study. Compared with the previous single-center study, our study will represent a more comprehensive and realistic assessment of the mobile-based lifestyle intervention effect among elderly population. In terms of limitations, considering the cost and feasibility, a 3-month intervention will be conducted which is short and the long-term effect may not be demonstrated. However, our finding will provide a preliminary data for the future studies with a longer-term intervention and follow-up. In addition, this study is designed as an open-labeled RCT because of the nature of the intervention which may cause bias. However, the outcome assessors and data analysts will be blinded to the group allocation and objective measures will be used as outcomes to minimize the bias. The Hawthorne effect will be avoided as much as possible through paying equal attention to the three groups.

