### 2.2. Study Design

This study is designed as a prospective, open-labeled, randomized, controlled and multi-center trial. Eligible subjects will be randomly assigned to three groups: the mobile-based nutrition and exercise intervention group (Group A), mobile-based exercise intervention group (Group B) and no intervention group (Group C). This study will assess parameters of glucose and lipid metabolism for three times. In addition, weight, height, waist circumference, hip circumference, blood pressure, C-reactive protein, liver enzymes, uric acid, copeptin, irisin, adiponectin, dietary data and physical activity data will also be evaluated at the same time. The study design is shown in Figure 1.

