### 2.4. Intervention

Volunteers allocated to Group A and B will have access to a health management app. The app has functions of recording and monitoring the participants’ diet and exercise daily. The interventions include mobile-based nutrition interventions and exercise interventions. 

The nutrition interventions require the subjects be provided with 20 g of the professional meal replacement powders (Huaruizhongjian Biotechnological Co., Ltd., Shandong, China), 200 mL milk and 5 mL flaxseed oil for their breakfast and dietary guidance based on Mediterranean diet for their lunch and supper. The meal replacement powders include 10 g of meal replacement powders rich in minerals (4.50 g protein, 0.09 g fat, 1.26 g carbohydrate and 3.00 g dietary fiber with 125 kJ in total energy) and 10 g of meal replacement powders rich in vitamins (4.65 g protein, 0.11 g fat, 1.05 g carbohydrate and 3.18 g dietary fiber with 126 kJ in total energy). The dietary guidance will be through individual sessions with nutritionists using mobiles, including healthy food choices and portion sizes, 3 to 5 times per week depending on the participants’ compliance. The diets will be tracked and recorded through uploading the food logs and pictures of their three meals per day using the health management app under the supervision of the investigators in the background. 

The exercise interventions require the subjects be provided with exercise guidance and complete around 20 min of aerobic exercise, 20 min of resistance exercise and at least 6000 steps every day. The exercise guidance will be through individual sessions with exercise instructors, including exercise choices, duration and intensity, 3 to 5 times per week depending on the participants’ compliance. If the participants feel a little tired after the exercise and comfortable for the next day, the exercise intensity will be the best. The everyday steps of the subjects will be tracked and recorded through the sports bracelet and the aerobic exercise and resistance exercise logs and pictures will be uploaded using the mobile app, which will be supervised by the investigators in the background. 

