Participants in Group A will receive nutrition interventions and exercise interventions for three months. Group B will receive exercise interventions for three months and Group C, the control group, will not be intervened and expected to follow their routine lifestyle as before. Interventions will be started one week after the enrollment.

The app and sports bracelet training will be provided in the same manner for both Group A and Group B volunteers one week before the start of this trial. The researchers will help the participants download the health management app through the smart phone app store and teach them to use the app and the sports bracelet. After the participants have learnt how to use the app and the bracelet, they will be asked to record their dietary data and physical exercise intensity following their old way of life for one week before the start of the intervention using the app and the bracelet, to guarantee that they have already grasped the usage of the app and the bracelet. As this is lifestyle intervention, the medication for the baseline chronic diseases will not be changed during the course of the study.

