#### 2.7.5. Dietary Data and Physical Activity Data

Dietary data and physical activity data will be measured at baseline, day 45 and day 90. Dietary data assessment will be based on the Food Frequency Questionnaire (FFQ), dietary logs and pictures on the app. The type, amount and frequency of food intake will be recorded by trained investigators. The amount of food will be estimated using the references of food models or photographic models [27]. Nutrients intake will be assessed using the Chinese Food Composition Table [28]. Physical activity will be assessed through the exercise logs, pictures and the average steps of 3 days before the baseline visit, day 45 and day 90 using the sports bracelet.

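### The protocol does not keep exercise-only Group B clear of app diet logging, a nutrition component, and its dietary outcome would be measured differently in Group C, which has no app

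*Protocol article*

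**What the plan says.** The protocol article assigns nutrition plus exercise to Group A, exercise to Group B and nothing to Group C (2.2). Section 2.4 repeats this for B: "Group B will receive exercise interventions for three months".

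Within 2.4, the nutrition paragraph covers the meal-replacement breakfast, dietary guidance and supervised food logging: "The diets will be tracked and recorded through uploading the food logs and pictures of their three meals per day using the health management app". The exercise paragraph lists only steps and exercise logs and pictures.

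The same section opens by giving both active arms one tool: "Volunteers allocated to Group A and B will have access to a health management app". It continues: "The app has functions of recording and monitoring the participants’ diet and exercise daily". No exercise-only version is described. Sections 2.4 and 2.6 have A and B record their usual diet in the app for one run-in week.

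Section 2.7.5 defines how the dietary outcome is obtained: "Dietary data assessment will be based on the Food Frequency Questionnaire (FFQ), dietary logs and pictures on the app". No group is named, and the outcome is scheduled for baseline, day 45 and day 90. In the Discussion, the paragraph on compliance turns first to Groups A and B and then has investigators "monitor their dietary and physical activity data and solve the problems they encounter in time".

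**The concern.** Section 2.4 makes supervised food logging part of what A receives and B does not. Other passages then give B the means to log (the shared app), a possible reason to log (app records as outcome data) and possible oversight of what is logged (the Discussion). With five cities carrying this out, one centre could have B log meals throughout and another could stop at day 0, and both could point to the text.

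Group B is what separates exercise from nutrition plus exercise. If it also receives diet self-monitoring, any benefit of that would be credited to exercise in B versus C and removed from nutrition in A versus B.

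A second problem does not depend on how B is read. Group C has no app, so a dietary outcome built from the questionnaire plus app records cannot be collected in the same way in all three arms.

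**Working it through.** **1. Who receives what**

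| Element | Where | Groups |
|---|---|---|
| Meal replacement and dietary guidance | 2.4, nutrition paragraph | A |
| Supervised food logs and meal pictures | 2.4, nutrition paragraph | A |
| App with diet recording and monitoring | 2.4, opening | A and B |
| Diet recording in the run-in week | 2.4; 2.6, Stage 1 | A and B |
| App food logs as dietary data | 2.7.5 | not stated |
| Investigators monitor dietary data | 4. Discussion | paragraph about A and B |

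Rows 2 and 3 do not fit together without a statement of what B does with the diet function after day 0. Rows 5 and 6 do not supply one.

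**2. What each contrast estimates**

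Let E be the exercise programme with its bracelet and contact, L app diet logging and monitoring, and N meal replacement plus guidance. Treat the effects as additive.

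- B stops logging at day 0: A = E + L + N and B = E, so A−B = L + N and B−C = E.
- B keeps logging: A = E + L + N and B = E + L, so A−B = N and B−C = E + L.

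Both sets are valid contrasts, but they answer different questions.

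**3. The plan's own sample size (2.8)**

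Inputs: mean BMI changes −2.8, −2.5 and −0.9 kg/m²; SD 1.4; alpha 0.05; power 0.90. The grand mean is −2.067 and the squared deviations sum to 0.538 + 0.188 + 1.361 = 2.087. The noncentrality is n × 2.087 / 1.96. One-way ANOVA power is 0.873 at n = 12 and 0.901 at n = 13, which reproduces 13 per group. Then 13 × 3 strata = 39, 39 × 5 centres = 195 (about 200), and 200 / 0.80 = 250.

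**4. How sensitive the contrasts are**

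Planned A−B is 2.8 − 2.5 = 0.3 kg/m² and planned B−C is 2.5 − 0.9 = 1.6 kg/m². Let d be the extra BMI loss in B from diet logging. The documents give no value, so d from 0 to 0.2 is an assumption. A is held at −2.8, and −2.5 is taken to exclude any logging effect.

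With 200 per group, the standard error of a difference is 1.4 × √(2/200) = 0.14. Unadjusted two-sided power at 0.05 is Φ((0.3 − d)/0.14 − 1.96).

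| d (kg/m²) | A−B | Power for A−B | B−C |
|---|---|---|---|
| 0 | 0.30 | 57% | 1.60 |
| 0.05 | 0.25 | 43% | 1.65 |
| 0.10 | 0.20 | 30% | 1.70 |
| 0.15 | 0.15 | 19% | 1.75 |
| 0.20 | 0.10 | 11% | 1.80 |

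Over this range the three-group ANOVA still needs only 12 or 13 per group for 90% power, and its power at 200 per group is essentially 100%.

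**5. Dietary outcome by arm**

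A has the questionnaire plus app records. B has the same if it logs, and otherwise the questionnaire alone. C has the questionnaire alone. C differs from A on either reading.

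**The case against.** The best defence is that the text can be read consistently. B's diet recording is explicit only for the run-in week, where it serves to teach the app and applies equally to A and B. From day 0, section 2.4 puts food logs under nutrition and exercise logs under exercise, which points to A alone logging meals. Section 2.7.5 may simply pool data sources: it does not exclude C either, and C plainly has no app. Arm-specific app settings are detail that an article may leave to the full protocol. B is also labelled a mobile-based exercise arm, so the app belongs to it by definition.

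Much of this stands. A reader might infer that investigators act on B's dietary data. The documents do not say so: the Discussion speaks of solving problems in a passage about compliance and difficulty with apps, and dietary guidance belongs to the nutrition intervention. A reader might also infer that neither pairwise contrast isolates anything. That goes too far: if both arms log, A versus B is a sound add-on comparison for meal replacement plus guidance. Switching logging off in B is therefore a design choice, not a necessary correction.

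The defence does not remove the conflict. The issue is more than silence about app settings: food logging sits in an A-only intervention, while the app, the outcome definition and the monitoring sentence are not limited to A. The point about C is untouched by it.

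**Conclusion.** The concern holds in limited form. The passages do not settle whether Group B logs diet after day 0. If it does, B versus C is exercise plus app diet self-monitoring, and A versus B is meal replacement plus guidance rather than the whole nutrition package.

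The size is unknown. The figures of 0.3 falling to 0.1 kg/m² and power falling from 57% to 11% illustrate how little room the planned A–B gap leaves. They rest on an assumed d, on A staying at −2.8 and on additivity, and d may be zero. It would be wrong to conclude that a third or two thirds of the nutrition effect will be lost, since that only divides an assumption by 0.3.

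Nor does it follow that the primary analysis fails. The primary outcome in Table 2 is the three-group BMI difference, no pairwise contrast is named as a target, and the sample size in 2.8 is unaffected. What is at stake is the interpretation of the pairwise differences and the comparability of the dietary outcome. The latter follows directly from C having no app.

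**What to change.** - In 2.7.5, make the food frequency questionnaire, administered by trained interviewers at days 0, 45 and 90, the dietary outcome in all three groups. Keep app food logs and pictures only as an adherence measure.
- Reconcile 2.4 with the Discussion by stating whether B logs diet after day 0 and what investigators do with any such records.
- Then either limit investigator diet monitoring to Group A, or describe B as exercise plus app diet self-monitoring and word the A–B and B–C conclusions to match.

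These are mainly changes of wording. The cost is that app diet logs no longer contribute to the dietary outcome in A and B. No change to the sample size or the primary test is needed.

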### 2.5. Follow-Up

All participants of this study will be followed-up for the duration of the intervention (three months). Participants may discontinue the trial at their request. If a participant does not meet the requirements of the study, he should also discontinue the trial. 

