### 2.6. Procedures

A summary of this trial is presented in Table 1. The study will consist of three stages:

Stage 1: from enrollment to the start of the intervention. At enrollment, eligible participants will sign informed contents and their basic information will be collected. Then they will be randomly divided into three groups (Group A, B and C). Participants in Group A and B will be taught how to use the app and sports bracelet by the researchers and required to record their diets and physical activities using the app and bracelet following their usual way of life for one week.

Stage 2: from the start of intervention (day 0) to day 44. On the morning of day 0, participants will be asked to arrive at the lab at 7:00 a.m. Measurements including anthropometry, body composition, blood pressure, fasting blood samples, dietary and physical activity data will be obtained based on standard procedures. Then, participants in Group A will receive mobile-based nutrition and exercise intervention. Participants in Group B will receive mobile-based exercise intervention. Participants in Group C will receive no interventions.

Stage 3: from day 45 to day 90. On the morning of day 45, measurements including anthropometry, body composition, blood pressure, fasting blood samples, dietary and physical activity data will be performed as day 0. Then, Group A and B will continue to receive their respective intervention and Group C will receive no intervention as before. On the morning of day 90, anthropometry, body composition, blood pressure, dietary and physical activity data will be measured and fasting blood samples will be collected for the third time. 

**Table 1 ijerph-18-04854-t001:** Summary of the trial.

Time Point	At Enrollment	After Allocation		
		Start (Day 0)	Day 45	Day 90
Enrolment				
Eligibility screen	√			
Informed consent	√			
Collection of basic information	√			
Randomization	√			
App and sports bracelet training	√			
Interventions (day 0-day 90)		√	√	√
Follow-up (day 0-day 90)		√	√	√
Assessments				
Anthropometry	√	√	√	√
Body composition (Inbody measurement)		√	√	√
Blood lipids		√	√	√
Fasting and postprandial blood sugar		√	√	√
Hemoglobin A1C		√	√	√
Blood CRP and insulin		√	√	√
Blood ALT and AST		√	√	√
Blood uric acid		√	√	√
Blood copeptin		√	√	√
Blood irisin		√	√	√
Blood adiponectin		√	√	√
Blood pressure		√	√	√
Dietary data		√	√	√
Physical activity data		√	√	√

CRP: C-reactive protein; ALT: alanine aminotransferase; AST: aspartic transaminase.

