### 2.8. Sample Size Calculation

The sample size was calculated for a one-way analysis of variance (ANOVA) comparing the mean change in between-group (three groups) BMI from preintervention to postintervention. According to related researches, the clinically meaningful difference in change in BMI was set to 1 kg/m^2^ and the mean change in BMI of the 12-week diet and exercise group, the 12-week exercise group and the control group was −2.8, −2.5 and −0.9 kg/m^2^, respectively. The standard deviation (SD) was assumed to be equal for all three groups and was set to SD = 1.4 Kg/m^2^ [29,30]. To obtain a power of 0.90 for the overall test of differences in means, using a significance level of 0.05, 13 individuals are required in each group. To account for the three stratification groups (age: 60~66, 67~73 and 74~80), a further 26 individuals are required. Considering the study will be conducted in 5 centers, approximately 200 individuals are required for each group. To account for 20% dropout, approximately a total of 250 individuals are required for each group. Calculations were performed using PASS statistical software Version 15.0.2 (NCSS, Kaysville, UT, USA).

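### Randomised participants who fail undefined requirements are withdrawn and their data eliminated, with no limit to a secondary analysis; the exclusions are likely to be unequal between arms and related to outcome

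*Protocol article*

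**What the plan says.** The quality-control text in the Discussion (Section 4) says: "If a participant fails to meet the requirements, their data will be eliminated and the reason will be recorded". Section 2.5 (Follow-Up) says: "If a participant does not meet the requirements of the study, he should also discontinue the trial". Neither place says what the requirements are.

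Section 2.6 and Table 1 put randomisation at enrolment, before the training week and day 0, so both rules act on people who already have an allocation.

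The tasks differ by arm:

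- **Groups A and B** (Section 2.4) are to "complete around 20 min of aerobic exercise, 20 min of resistance exercise and at least 6000 steps every day", upload exercise logs and pictures, and take part in guidance sessions 3 to 5 times per week. In the week before day 0 they are also "required to record their diets and physical activities using the app and bracelet following their usual way of life for one week" (Section 2.6).
- **Group A** in addition has the supplied breakfast, dietary guidance, and logs and pictures of three meals a day (Section 2.4).
- **Group C** "will not be intervened and expected to follow their routine lifestyle as before" (Section 2.4). Like the other arms, it has the visits and blood samples of days 0, 45 and 90.

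Section 2.3 says that participants and study investigators cannot be blinded, whereas outcome assessors are. Section 2.9 plans a one-way ANOVA or Kruskal-Wallis test and names no analysis population. The Discussion lists reduced selection bias through randomisation as a strength.

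**The concern.** Randomisation protects the comparison only if the people analysed are the people randomised, or if losses are unrelated to arm and outcome. Here the plan itself creates losses, on a criterion that is harder to meet in A and B than in C. People who keep up daily exercise and logging probably differ in motivation from those who do not, and motivation may predict BMI change even where the intervention does nothing. Removing the less adherent from A and B while C stays nearly whole would compare selected with unselected people.

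Two features make this harder to repair. The criterion is undefined, and adherence is supervised by unblinded investigators, so its application is discretionary. Withdrawal under Section 2.5 would also end outcome measurement, so the effect of the exclusions could not be checked later. The Discussion promises covariate adjustment, but adjusting for measured factors cannot be relied on to remove selection on motivation.

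**Working it through.** **1. The plan's own figure (Section 2.8).** Inputs: mean BMI changes −2.8, −2.5 and −0.9 kg/m², SD 1.4, alpha 0.05, power 0.90. The noncentral F distribution gives power 0.901 at 13 per group (0.873 at 12), so 13 reproduces. Then 13 + 26 = 39 for three age strata, 39 × 5 centres = 195 (about 200), and 200/(1 − 0.20) = 250. The sample size is not affected by this point.

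**2. Inputs for the illustration.** From the document: SD of BMI change 1.4 and 250 randomised per arm. Assumed, because the document gives neither: the fraction *q* eliminated in A and B, and the correlation *r* between poor adherence and BMI change. Also assumed: no true effect, no elimination in C, no other dropout.

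**3. Spurious difference from C.** If the least adherent fraction *q* is removed, under a normal model:

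shift = r × 1.4 × φ(c)/(1 − q), with c the (1 − q) normal quantile.

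For q = 0.20: c = 0.842, φ(c) = 0.280, so shift = r × 1.4 × 0.280/0.80 = 0.49r. This gives 0.049, 0.098, 0.147 and 0.245 kg/m² for r = 0.1, 0.2, 0.3 and 0.5, in the direction of more BMI loss.

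**4. Set against the standard error.** With 200 left in an intervention arm and 250 in C, SE = 1.4 × √(1/200 + 1/250) = 0.133. The shifts are 0.37, 0.74, 1.11 and 1.85 SE.

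**5. Type I error of the planned three-group ANOVA.** Simulation with 4,000 runs per cell, deletion in A and B only; each cell shows shift (kg/m²) / rejection rate:

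| q | r = 0.1 | r = 0.2 | r = 0.3 | r = 0.5 |
|---|---|---|---|---|
| 5% | 0.015 / 0.05 | 0.030 / 0.05 | 0.046 / 0.06 | 0.076 / 0.09 |
| 10% | 0.027 / 0.05 | 0.055 / 0.07 | 0.082 / 0.10 | 0.136 / 0.19 |
| 20% | 0.049 / 0.07 | 0.098 / 0.11 | 0.147 / 0.21 | 0.245 / 0.50 |
| 30% | 0.070 / 0.07 | 0.139 / 0.17 | 0.209 / 0.34 | 0.348 / 0.80 |

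Without deletion the shift from this source is 0 and the rate is 0.05.

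**6. Set against the planned effects.** A−C: 2.8 − 0.9 = 1.9. B−C: 2.5 − 0.9 = 1.6. At q = 20%, 0.049 to 0.245 is 3% to 13% of 1.9 and 3% to 15% of 1.6.

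**The case against.** The strongest defence is that the requirements may concern data quality only. The sentence before the elimination rule is about training participants in the questionnaires and procedures, and the neighbouring text deals with duplicate measurements and sample storage. Elsewhere the article seems to expect poor adherers to stay: session frequency depends on compliance (Section 2.4), and the Discussion says poor app use may reduce the effect. This shows a real ambiguity but does not remove the problem. The preceding sentence also names the requirements of the trial as a whole, the paragraph opens with compliance in A and B, and Section 2.5 ties nearly the same words to leaving the trial. An analysis plan that is not shown could add detail, but analysis as randomised would contradict the elimination sentence as it stands.

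A reader might infer that requirements exist only in A and B. The document does not support that. C has visits, fasting and postprandial blood samples, dietary assessment and a routine-lifestyle expectation. Nor must B log food daily during the intervention: meal logging belongs to the nutrition component, which only A receives, and B's explicit diet-recording duty is the one week before day 0. If C also loses people, the net shift is the difference between arms. With the same r = 0.3, 20% removed in A and 10% in C leaves 0.147 − 0.082 = 0.065 kg/m².

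The error rates rest on assumed inputs. The 20% happens to equal the allowance in "To account for 20% dropout, approximately a total of 250 individuals are required for each group", but the article treats quitting separately from elimination and gives no elimination rate. With no true effect, *r* can come only from background traits, so 0.5 is a high value. The rates also apply to BMI change. For raw day-90 BMI, the outcome as worded in Table 2, the SD may be larger and the inflation correspondingly smaller.

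**Conclusion.** The point stands: the article commits to withdrawing randomised participants and eliminating their data on an undefined criterion that bears mainly on A and B, without limiting this to a secondary analysis. Following it can bias the primary comparison and undermines the stated strength of reduced selection bias.

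Favouring A and B over C is the most plausible direction, not a certainty. On the assumptions shown, with 20% eliminated in A and B and none in C, the spurious difference is about 0.05 to 0.25 kg/m² and the ANOVA type I error about 0.07 to 0.50, lower with fewer eliminated. These figures illustrate the mechanism and do not predict what the trial will show.

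Two stronger readings are not supported. One is that the bias would account for the effect the trial expects: on these assumptions it is small against 1.9 and 1.6 kg/m², and matters for the conclusion mainly if the true effect is near zero. The other is that it threatens the planned A−B difference of 2.8 − 2.5 = 0.3 kg/m² to the same degree. The shift calculated here is against C, and if A and B lose similar people it largely cancels between them.

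**What to change.** - Remove the elimination rule from the primary analysis. State that all randomised participants with available data are analysed in their allocated group, whatever their adherence.
- Reword Section 2.5 so that failing the requirements or stopping the intervention does not end the scheduled day-45 and day-90 measurements, unless consent is withdrawn. This concerns data collection only; it takes no position on who should continue the intervention.
- Define the requirements. If the elimination sentence was meant only for unusable questionnaires or samples, say so, and apply it to the affected item in all arms alike.
- Keep any analysis of compliers as a labelled sensitivity analysis with its criterion fixed in advance.

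A repeated-measures model using the day-45 BMI, so that people without a day-90 value still contribute, is optional.

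The cost is wording in two places and attendance at visits already scheduled by people who stop the intervention. The sample size does not change. The effect estimate may be somewhat smaller.
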